#### Insecticide resistance assessment

2.13.3

Insecticide resistance survey was conducted during the baseline surveys only. Breeding sites were mapped from the 20 candidate clusters from May–July 2019. Larvae were collected from multiple breeding sites from candidate clusters and reared to adults in the insectary of Amani centre, Muheza, NIMR. Resistance assays were carried out using WHO cylinder test for adult mosquitoes with impregnated papers obtained from the WHO supplier at Universiti Sains Malaysia. Impregnated papers were stored at 4 °C and used no more than twice and two common pyrethroids were tested at diagnostic doses (permethrin 0.75 % and deltamethrin 0.05 %) as defined by the WHO [33]. Two to five-days old female *An. gambiae* s.l. mosquitoes were tested using WHO cylinder test kit with four replicates of 15–25 wild adult female mosquitoes per cylinder. During the exposure period, knock-down (KD) rates were recorded after exposure times of 10, 15, 20, 30, 40, 50 and 60 min. A mosquito was considered knocked down if it laid on its side on the floor of the exposure tube and was unable to fly. At the end of the exposure period, mosquitoes were transferred into holding tubes (lined with untreated papers) by gently blowing them through the open space between the exposure tube and the holding tubes. Cotton soaked in 10 % sugar was placed on top of the holding tube. The mortality was scored 24 h post-exposure. The susceptibility status was evaluated based on the WHO criteria, i.e. a 98–100 % mortality indicated susceptibility; 90–97 % mortality required confirmation, and mortality below 90 % indicated resistance [33]. When the control mortality between 5 % and 20 % was recorded, the mean observed mortality was corrected using Abbott's method [34]. Surviving and dead mosquitoes were analyzed for species identification and knockdown resistance status (presence of L1014S *kdr*E alleles) using TaqMan assay as described previously [35].

#### Social perspectives investigation

2.13.4

A multi-sited intrinsic case study approach was adopted to explore community perceptions and their experiences of living with the 3D-WDS, as well as the experiences of installers involved in installing the 3D-WDS in houses. This method was chosen because of its capacity to delve into individual and community living experiences in detail, to determine how these perceptions and experiences changed over time, both before and after the installation of the 3D-WDS. A purposeful sampling approach was employed to select three clusters out of seven intervention clusters that were offered 3D-WDS. Community members from the study clusters were invited to participate, and a convenience sampling method was used to select those who were present at home. Three focus groups were formed, the first focus group with male members from the study clusters (3 male focus groups from 3 clusters), the second focus group with female members from the study clusters (3 female focus groups from 3 clusters), resulting in a total of 6 FGDs across 3 study clusters. Additionally, all 7 head installers from their respective study clusters were invited to form a focus group. A total of 7 FGDs were conducted. All interviews were recorded using a digital voice recorder (Sony ES404) and the recorded interview audios were transcribed verbatim and read thoroughly several times and coded using a deductive approach to data analysis, whereby codes were influenced by research questions [36]. Thematic content analysis was applied to categorize and code the interview transcripts, whereby utterances of one participant were compared to another and later across clusters to identify common themes [[37], [38], [39]]. From each common theme, perceptions and experiences reported by all participants were specifically examined to allow formulation of patterns including main theme and sub-themes. Additionally, approximately half of the residences that were offered 3D-WDS across all 7 intervention clusters were chosen randomly for interviews with the head of the household. Interview questions were structured and organised to address topics such as common household practices to manage mosquitoes, 3D-WDS design aesthetics and durability, ease of handling and maintenance, integrity over time, installation quality, choice of materials and any additional recommendations. Interview responses were captured using ODK forms uploaded on Android tablets.

#### Data management

2.13.5

Trained field workers used standardised data entry forms on an Android tablet (Samsung) with the Open Data Kit (ODK) Collect app to input data, which was then directly sent to a secure cloud server. The study coordinator was responsible for ensuring data validation and routine monitoring to identify any incomplete, missing, inconsistent or inaccurate data, including typos and technical errors. The project PIs closely monitored the data collection and processing through the electronic server, while the field workers had no access to the collected data. In case of technical difficulties with the electronic devices in the field, a hard copy of the respective electronic form was provided to the field workers. The data was entered into the computer with only codes of households and no names, so that they were not identifiable by the data entry clerks. The study did not and will not reveal the identity of individual participants in any reports or publications. The electronic servers, where the data was stored, were password-protected, with access granted only to the study coordinator, data management staff and project PIs. Hardcopies of data, protocol, SOPs and other documentations were kept in locked filing cabinets and only accessible to authorised study personnel. The documents will be held for at least 10 years at the host institution.

### Statistical methods

2.14

#### Outcome variables

2.14.1

Intervention epidemiological outcomes for the at-risk children will be assessed for one primary outcome and one secondary outcome at the level of individual health. The primary outcome will be malaria prevalence, a binary variable measured as the mRDT test result. The secondary outcome will be haemoglobin level, a strong correlate of recurring malarial episodes, as a continuous variable measured as concentration g/dl using the HemoCue analyser.

To examine whether 3D-WDS could influence entomological parameters, we will test for intervention effects on indoor mosquito densities, measured as the number of mosquitoes captured in CDC-LTs per night, and the entomological inoculation rate (EIR), measured as the number of infective bites per person per unit time, both as secondary outcomes.

#### Baseline patterns

2.14.2

We will investigate the baseline surveys to understand two different patterns [1]: whether any demographic or health variables differed systematically between control and intervention clusters [2]; which demographic and geographic variables were associated with the outcome variables, before any intervention was made. The following variables will be compared between control and intervention clusters: age, gender, malaria prevalence, haemoglobin levels, indoor mosquito densities and EIR. These variables will be tested in a (generalized) linear mixed model with the demographic/health variables as the response variables and cluster type as the only predictor. For the baseline models for patient outcomes, the following variables will be examined as predictors: age, gender and distance to nearest health centre. These three variables will be fitted in a single model, which will be then simplified stepwise by removing any predictors with p > 0.05 until only significant predictors remain.

#### Intervention effects

2.14.3

Intervention effects on patient outcomes will be assessed in a multivariate model that also includes the baseline variables specified above, including controlling for age and monthly precipitation squared. These intervention models will use data from all post-intervention surveys and will include time since baseline as a predictor variable, to allow for potential gradual or cumulative effects over the course of follow-up. Intervention/control will be included in these models as a main effect and also in interaction with time, allowing outcomes to change through time in one group but not in the other (e.g. a gradual decrease in malaria prevalence in intervention clusters vs. no change in control clusters). If the interaction will not be significant, it will be removed from the model and the main effect of intervention assessed.

In addition, we will test for any overall or intervention-driven change from baseline to post-intervention by pooling all post-intervention surveys and testing for an interaction between intervention. Due to the distribution of bed nets as part of the protocol, it will be possible that all participating households would experience a reduction in epidemiological or entomological outcomes, but that the reduction would be even bigger for households receiving 3D-WDS intervention.

#### Model structure

2.14.4

All statistical modelling will be done with mixed-effects models, using the lme4 package in R [40]. All models of patient outcomes will include a random effect (random intercept) of household nested within cluster. This will allow for non-independence of sampling units by allowing the response variable to vary between clusters and in addition between households, not in association to any of the modelled fixed effects but in relation to any unobserved sources of structured error. Child ID will not be included as a random effect because the spontaneous nature of which children each household presented for examination at each visit meant that few children will be resampled often enough to be able to informatively model the individual-level variation. Baseline models will be fitted using only cluster ID as the random effect, due to limited sample sizes within each household. Malaria prevalence as measured by mRDT will be modelled in a binomial model with a logit link, and haemoglobin level will be modelled in a Gaussian model with an identity link.

Indoor mosquito densities and EIR will be analyzed at the level of clusters, using total counts of 24-night CDC-LTs collections per cluster in every cross-sectional survey. Hence, the models will include only a random effect (random intercept) of cluster ID. Count data will be modelled in a Poisson model with a log link; potential overdispersion will be accounted for by including an observation-level random effect. EIR will be modelled in a binomial model with a logit link weighted by the number of mosquitoes caught in each sample.

Community members’ perceptions will be qualitatively analyzed using data from questionnaires, focus group discussions and in-depth interviews. Additionally, quantitative data from the household questionnaire survey will be summarised using appropriate descriptive statistics.

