**Primary outcome**		
Malaria prevalence	mRDT	Cross-sectional surveys at baseline and 10, 20, 30, 40 and 50 (±2) weeks post installation

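### The binomial EIR model has no term for scatter between surveys within a hamlet, so its before/after test is too liberal if such scatter exists

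*Protocol article*

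**What the plan says.** Section 2.14.4 (Model structure) of the protocol article treats indoor density and EIR together, at hamlet level, "using total counts of 24-night CDC-LTs collections per cluster in every cross-sectional survey". Of both it says: "Hence, the models will include only a random effect (random intercept) of cluster ID". It then names one addition, for the Poisson count model: "potential overdispersion will be accounted for by including an observation-level random effect". The next sentence sets the other model: "EIR will be modelled in a binomial model with a logit link weighted by the number of mosquitoes caught in each sample". No overdispersion term is attached to it there or elsewhere in the article.

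Section 2.14.3 (Intervention effects) plans a before/after analysis: "we will test for any overall or intervention-driven change from baseline to post-intervention by pooling all post-intervention surveys". The sentence stops before naming the second term of the interaction; I read it as arm by period. The reason given for the test covers mosquito outcomes too, since it foresees that, because of the nets, "all participating households would experience a reduction in epidemiological or entomological outcomes". Table 2 sets the survey times, which apply to EIR as well: "Cross-sectional surveys at baseline and 10, 20, 30, 40 and 50 (±2) weeks post installation".

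**The concern.** Both outcomes come from the same traps and the same rows, yet only one of the two models may show more variation than its distribution implies. In a grouped binomial model, the proportion and the denominator fix the variance. With a hamlet intercept and nothing else random, all mosquitoes tested in one hamlet at one survey count as independent draws from a proportion that can change over time only through the fixed effects.

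The article gives reason to doubt this. Section 2.1 (Study setting) describes two seasonal mosquito peaks, with *An. gambiae* s.l. declining towards the dry season while *An. funestus* remains common. Section 2.13.2 tests both for sporozoites. If the species mix shifts at different times in different hamlets, the sporozoite proportion will move between surveys within a hamlet.

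The tests exposed are those that compare surveys within hamlets: the overall before/after change and its difference between arms. At stake is a claimed fall in infective mosquitoes under the screens that is only hamlet-by-survey scatter, and that would look like support for the mechanism.

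**Working it through.** **Inputs from the protocol article.** 14 hamlets, 7 per arm; 6 surveys (baseline and 5 follow-up), so 14 × 6 = 84 records; 24 trap-nights per hamlet per survey; 3.2 *Anopheles* per night at baseline; CV 0.5; a 63% decrease; 5% significance and 80% power (section 2.9).

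**The plan's own figure.** No error rate is stated for the EIR model. The density design uses the same catch inputs and reproduces with the Hayes-Bennett formula for rates. With a control rate of 3.2, an intervention rate of 3.2 × 0.37 = 1.184 and (1.96 + 0.842)² = 7.85:

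1 + 7.85 × [(3.2 + 1.184)/24 + 0.25 × (3.2² + 1.184²)] / (3.2 − 1.184)² = 1 + 7.85 × (0.183 + 2.910)/4.064 = 6.97, that is 7 hamlets per arm, as planned.

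**Assumptions.** Sporozoite rate p of 1, 3 or 5%; hamlet-by-survey SD s of 0.3, 0.5 or 0.8 on the logit scale; n = 24 × 3.2 = 76.8 mosquitoes per record, or 76.8 × 0.37 = 28.4 if catches fell by the design's 63%.

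**Formula.** The log-odds of one record has variance of about 1/[n p(1−p)] under the binomial model, and that plus s² when there is scatter. The ratio is D = 1 + n p(1−p) s². With equal records, D carries over to any contrast within hamlets, and the true size of a nominal 5% test is 2[1 − Φ(1.96/√D)]. Example with n = 76.8, p = 3%, s = 0.5: D = 1 + 76.8 × 0.0291 × 0.25 = 1.56, and 1.96/√1.56 = 1.57, giving 11.6%.

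**Arm-by-period test, n = 76.8.** The last column is from simulated null trials (hamlet SD 0.4, binomial model with hamlet effects, Wald test).

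| p | s | D | Formula | Simulated |
|---|---|---|---|---|
| 1% | 0.3 | 1.07 | 5.8% | 5% |
| 1% | 0.5 | 1.19 | 7.2% | 7% |
| 1% | 0.8 | 1.49 | 10.8% | 11% |
| 3% | 0.3 | 1.20 | 7.4% | 6% |
| 3% | 0.5 | 1.56 | 11.6% | 12% |
| 3% | 0.8 | 2.43 | 20.9% | 28% |
| 5% | 0.3 | 1.33 | 8.9% | 8% |
| 5% | 0.5 | 1.91 | 15.6% | 17% |
| 5% | 0.8 | 3.33 | 28.3% | 35% |

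The formula is a first-order approximation and falls short at the largest SD. With no scatter, the simulated rate is about 5%.

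**Same formula, n = 28.4.** For s = 0.3 / 0.5 / 0.8: 5 / 6 / 7% at p = 1%, and 6 / 7 / 11% at p = 3%.

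**Check with the planned model form.** A binomial mixed model with a random hamlet intercept was fitted by maximum likelihood with likelihood-ratio tests, 800 null runs per setting and catches varying around 76.8:

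- No scatter: arm by period 4.5-6.9%, overall before/after 5.4-6.4%.
- s = 0.5, at p = 1 / 3 / 5%: arm by period 11.2 / 16.4 / 21.2%, overall 11.8 / 18.1 / 23.0%.
- s = 1.0: arm by period 25.6 / 41.5 / 48.5%, overall 30.8 / 44.5 / 51.5%.
- With an observation-level random effect added: arm by period 4-8%, overall 5-8%, in all settings.
- Post-intervention arm main effect, model as written: 7-8% with no scatter, 6-10% at s = 0.5, 8-15% at s = 1.0.
- Arm by time in the post-intervention surveys, if run: 10-20% at s = 0.5, 27-49% at s = 1.0.

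**The case against.** **The inflation is conditional.** It needs real extra-binomial scatter, and the article reports none for sporozoite results. This stands. A reader might infer that the EIR tests will reject too often; the article supports only that they will if scatter is present.

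**The catch of 77 may be high.** The 3.2 per night comes from a June-July baseline, inside the April-September mosquito peak. It counts *Anopheles*, while only female *An. gambiae* and *An. funestus* go to sporozoite PCR. Nets were then topped up in both arms. This stands too, and is why the smaller catch is shown.

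**The scope is narrow.** A reader might extend the problem to an arm-by-time test for EIR, but section 2.14.3 writes that model for patient outcomes. Only the before/after paragraph mentions mosquito outcomes. A reader might also extend it to the post-intervention comparison of arms, which the simulations show is much less affected. EIR is one of several secondary outcomes, and the primary outcome is untouched.

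**The wording may be silence rather than exclusion.** The statement that the models hold only a hamlet intercept covers both outcomes, and the next sentence relaxes it for counts. It may therefore be meant as a contrast with the household-within-hamlet structure of the patient models. On that view the EIR sentence is simply incomplete, and dispersion handling could sit in a fuller analysis plan. This is fair as to intent. But the article does not leave the EIR model open: it fixes distribution, link, weights and random effects, and gives the extra term to its companion alone. Followed as written, the EIR model omits it.

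**Conclusion.** The point holds in conditional form. The EIR model as specified makes no allowance for scatter between surveys within a hamlet, although the density model on the same records does. If the sporozoite proportion varies beyond binomial error, which the described seasonal and species shifts make plausible, the baseline versus post-intervention test for EIR, overall and by arm, is too liberal.

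The size ranges from negligible (a 1% rate, small catches or little scatter) to a false-positive rate of about one in three (a 5% rate, 77 mosquitoes per record, SD 0.8). A middle case of 3% and SD 0.5 gives about 12%, or 16% in the mixed-model check with varying catches. All of these rest on assumed rates and scatter.

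A reader might also infer that the problem follows whatever form the EIR analysis takes. It does not: if infective mosquitoes are modelled as counts, the article's overdispersion provision for counts already applies.

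**What to change.** In section 2.14.4, give the binomial EIR model the same observation-level (hamlet-by-survey) random effect as the count model, or specify a beta-binomial. If the outcome is recast as a count of infective mosquitoes, no further overdispersion term is needed.

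The cost is one extra variance parameter and somewhat wider intervals if scatter is present. If there is none, the variance should be estimated near zero with little loss. No new data are needed, and the trial status section says statistical evaluations are still under way.

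The term does not absorb a shock shared by all hamlets in one survey. For the overall before/after change, that would need a survey effect.

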### Monitoring

2.15

The University of Helsinki served as the trial sponsor and primary coordinating centre, overseen by the chief investigator and co-investigators. Meanwhile, NIMR, AMRC functioned as the local coordinating centre, comprising local investigators, an experienced management team, field entomologists and laboratory technicians. A co-investigator from the primary coordinating centre, along with local co-investigators, directed trial activities, implemented the field study protocol, managed day-to-day operations under the chief investigator's supervision, and ensured that data collection adhered to standard operating procedures (SOPs). SOPs were developed based on Good Clinical Practice (GCP) and Good Field Entomology Practice (GFEP). Study investigators held weekly meetings to assess trial progress, while a Trial Steering Committee (TSC), consisting of key researchers from Finland and Tanzania, including the principal investigator (PI) and co-PIs, met remotely after each survey to oversee data collection and review overall trial progress.

## Discussion

3

Efforts to manage malaria in sub-Saharan Africa over the last two decades have successfully averted numerous clinical cases. The widespread use of LLINs and IRS has been pivotal in reducing malaria-related deaths. However, the ongoing rise in insecticide-resistant mosquitoes and drug-resistant parasites poses a threat to the sustained effectiveness of these control measures. There is a clear imperative to invest in the research and implementation of alternative vector control strategies that do not rely on insecticides, are environmentally friendly, sustainable and socially acceptable.

The 3D-Screen offers a non-insecticidal alternative that addresses the urgent demand for novel vector control methods. These screens can be easily incorporated into existing window frames, requiring minimal structural adjustments. This provides a durable and effective complement to existing vector control measures including LLINs, IRS, coils and other repellents, without the need for their discontinuation or replacement.

The project has been designed to test whether using 3D-WDS in windows of houses, in addition to LLINs, provides additional protection against malaria mosquitoes through a large-scale cRCT in the selected communities of Muheza, Tanzania. The primary outcomes of the study will provide information about the efficacy of screening windows with 3D-WDS and trapping host-seeking malaria vectors on malaria prevalence, indoor mosquito densities and EIR. Baseline data collection will enable comparisons before and after the intervention, while separating intervention clusters by sufficient distances (≥2 km) will minimize potential spill-over effects, ensuring an effective evaluation of the impact of 3D-WDS. With extensive coverage (>80 %) of 3D-WDS in the intervention clusters, baseline measurements and a follow-up period of 50 weeks will track its gradual effectiveness. Comprehensive data collection focused on various outcomes, including malaria prevalence, indoor vector densities, EIR and community acceptance. This approach will provide a thorough understanding of the 3D-WDS's impact from multiple perspectives. Insights gained will be crucial for optimizing future scaling-up efforts and informing improvements for more effective designs, even if no significant effects are observed.

Creating a physical barrier between mosquitoes and hosts effectively protects against mosquito-borne diseases. Traditionally, house screening involves fitting mosquito screens to windows and doors to prevent mosquito entry. The 3D-WDS is a novel mosquito screen that not only blocks mosquito entry but also traps mosquitoes attempting to enter or escape from the house after a successful blood meal. Widespread use of 3D-WDS could therefore reduce mosquito numbers, blood-engorged mosquitoes in communities and reduce malaria transmission.

However, achieving high community coverage for such interventions remains a challenge. To address this, the study involved community members, including local carpenters and house owners in the installation process of the 3D-WDS. This approach helped to foster a sense of ownership, enhance health awareness and encourage the adoption of the new intervention. Engaging the community in these ways could ultimately contribute to reducing disease incidence and improving the effectiveness of the intervention.

